### **2.1.1 PI'S QUALIFICATIONS & AGREEMENTS**

1. The investigators should be qualified by education, training, and experience to assume responsibility for the proper conduct of the trial at their site and should provide evidence of such qualifications through an up-to-date curriculum vitae and/or other relevant documentation requested by the Sponsor, the research ethics committee (REC), the institutional review board (IRB), and/or the regulatory authority(ies).
2. The investigator should be thoroughly familiar with the appropriate use of the investigational product, as described in the protocol, the product information and in other information sources provided by the Sponsor.
3. The investigator should be aware of, and should comply with, the principles of ICH GCP and the applicable regulatory requirements. A record of GCP training should be accessible for all investigators.
4. The investigator/site should permit monitoring and auditing by the Sponsor, and inspection by the appropriate regulatory authority(ies).
5. The investigator should maintain a delegation log of appropriately-qualified persons to whom the investigator has delegated significant trial-related duties.
6. The investigator should sign an investigator statement, which verifies that the site is willing and able to comply with the requirements of the trial.

### **2.1.2 ADEQUATE RESOURCES**

1. The investigator should be able to demonstrate a potential for recruiting the required number of suitable subjects within the agreed recruitment period (that is, the investigator regularly treats the target population).
2. The investigator should have sufficient time to properly conduct and complete the trial within the agreed trial period.
3. The investigator should have available an adequate number of qualified staff and adequate facilities for the foreseen duration of the trial to conduct the trial properly and safely.
4. The investigator should ensure that all persons assisting with the trial are adequately informed about the protocol, the investigational products, and their trial-related duties and functions.
5. The site should have sufficient data management resources to allow prompt data return to the co-ordinating centre (refer to the Data Management Plan for timelines). Sites that have previously participated in trials coordinated by the same centre should have a proven track record of good data return.

### **2.1.3 SITE ASSESSMENT**

Each selected clinical trial site must complete the AMBITION-*cm* EDCTP Consortium Agreement, Accession Form, Signature and Delegation of Responsibilities Log, and staff contact details. The Accession Form verifies that the site is willing, and able to comply with the requirements of the trial. In addition, and in compliance with the principles of ICH GCP, all site staff participating in the trial must complete the Signature and Delegation of Responsibilities Log and forward this to the co-ordinating centre. The co-ordinating centre must be notified of any changes to trial personnel and/or their

responsibilities. An up-to-date copy of this log must be stored in the Trial Master File (TMF) at the site and at the co-ordinating centre.

## 2.2 SITE/INVESTIGATOR EXCLUSION CRITERIA

Failure to meet the above requirements.

## 2.3 APPROVAL AND ACTIVATION

The ethics committees/Institutional Review Boards of the participating institutions will be supplied with the names and addresses of all participating site principal investigators. Trial staff at the co-ordinating centre will perform this task; hence it is vital to receive full contact details for all investigators prior to their entering patients.

1. The site should conduct the trial in compliance with the protocol as agreed by the Sponsor and, if required, by the regulatory authority(ies), and which has been approved by the REC and/or IRB.
2. The PI or delegate should document and explain any deviation from the approved protocol, and communicate this with the trial team at the co-ordinating centre.

A list of activated sites may be obtained from the Trial Manager.

## 2.4 SITE MANAGEMENT

The Cape Town site is led by the highly experienced and long-standing cryptococcal trialist [name], based at the University of Cape Town, who has been an investigator on numerous cryptococcal treatment trials, and was a lead investigator on the multi-centre trial of ART timing recently published in the NEJM. The Botswana site, based at the Botswana-Harvard Partnership, has successfully conducted a number of clinical trials of CM treatments, recruited patients for the phase-II EFA study, and has an effective study team already in place. The Zimbabwe team led by [name] and [name], based at the University of Zimbabwe, performed and published one of the seminal studies investigating ART timing in CM, and is currently performing studies investigating the utility of cryptococcal antigen screening as a strategy to prevent CM. The two proposed Malawian sites (College of Medicine / Malawi-Liverpool Wellcome Trust Clinical Research Programme and UNC-Project Malawi) both have on-going active CM research programmes, and have built considerable local expertise in the conduct of cryptococcal clinical trials. The Investigators at the Ugandan site, based at the Infectious Diseases Institute, have recently completed an NIH- funded trial of ART timing after Cryptococcal meningitis and a CDC-funded trial for cryptococcal antigen screening to improve ART survival, and are currently running an NIH and UK Medical Research Council co-funded trial to determine the utility of Sertraline as adjunctive therapy for cryptococcal meningitis. All sites have agreed to and are fully committed to study participation.

## SELECTION OF PATIENTS

There will be **no exceptions** to eligibility requirements at the time of randomisation. Questions about eligibility criteria should be addressed prior to attempting to randomise the participant.

The eligibility criteria for this trial have been carefully considered. The eligibility criteria are the standards used to ensure that only medically appropriate patients are considered for this study. Patients not meeting the criteria should not join the study. For the safety of the patients, as well as to ensure that the results of this study can be useful for making treatment decisions regarding other patients with similar diseases, it is important that no exceptions be made to these criteria for admission to the study.

Participants will be considered eligible for enrolment in this trial if they fulfil all the inclusion criteria and none of the exclusion criteria as defined below.

### 3.1 PATIENT INCLUSION CRITERIA

1. Consecutive patients aged  $\geq 18$  yrs with a first episode of cryptococcal meningitis (CSF India ink or CrAg test)
2. HIV positive or willing to undertake an HIV test if unknown HIV status
3. Willing to participate in the study or, if unable to consent, has a next of kin who agrees to the patient participating in the study

### 3.2 PATIENT EXCLUSION CRITERIA

1. Pregnancy (confirmed by urinary or serum pregnancy test) or breastfeeding
2. Previous serious reaction to amphotericin, flucytosine or fluconazole
3. Already taking antifungal treatment at cryptococcal meningitis treatment doses (amphotericin B  $\geq 0.7$ mg/kg or fluconazole  $\geq 800$ mg/day) for  $>48$  hours
4. Contraindicated concomitant medications including: cisapride and the class of antihistamines including terfenadine.
5. HIV negative

### 3.3 NUMBER OF PATIENTS

850 patients (425 per arm)

850 patients will be enrolled (425 in the control arm and 425 in the short-course L-AmB). The intake will take place over a 3-year period (see [Section 2](#)), and follow-up will occur for 16 weeks after the start of treatment. The total duration of the study will be 39 months.

### 3.4 CO-ENROLMENT GUIDELINES

Co-enrolment in previous or future trials is considered in [Section 4.3 Co-enrolment Guidelines](#).

### 3.5 SCREENING PROCEDURES & PRE-RANDOMISATION INVESTIGATIONS

Patients over 18 years of age with a first episode of cryptococcal meningitis diagnosed based on CSF India ink or cryptococcal antigen test at the local laboratory will be assessed for eligibility for inclusion in the trial. Their details will be recorded in a screening register. Patients will be enrolled into the study based on the criteria of eligibility outlined in [sections 3.1 and 3.2](#). For those found to be ineligible the reason for non-inclusion should be recorded on the screening register.

Written informed consent to enter the trial and be randomised must be obtained from participants or, in the case of those lacking capacity to consent, from family/guardians/person with legal responsibility (if appropriate and in keeping with National guidance and regulations), after explanation of the aims, methods, benefits and potential hazards of the trial, and BEFORE any trial-specific procedures are performed or any blood is taken for the trial (see Consent Forms).

Patients with altered mental status who are unable to consent will be enrolled into the study if their next of kin gives informed consent or assent (in keeping with appropriate National guidance and regulations) on their behalf. As soon as the patient's mental status improves consent will be obtained as above, with care taken to ensure they understand that they are free to withdraw from the study and if they do so this will not jeopardise their future care.

It must be made completely and unambiguously clear that the participant (or guardian) is free to refuse to participate in all or any aspect of the trial, at any time and for any reason, without incurring any penalty or affecting their access to the standard treatment available at the recruiting site (or that of their relative).

Original signed consent forms must be kept by the investigator and documented in the electronic case report form eCRF, a copy given to the participant or family, and a copy placed in the participant's medical notes.

## REGULATION & RANDOMISATION

Patients will be randomised individually using a computer-generated programme. Randomisation will be stratified by site.

### 4.1 RANDOMISATION PRACTICALITIES

Further details on the process of randomisation can be found in [Section 9.1 - Method of Randomisation](#).

#### RANDOMISATIONS

To randomise:

Upon confirmation of eligibility criteria and completion and entry of the informed consent details, the electronic data capture system (EDC) will select the next available randomization slot and present the details of the selection to the Study Doctor / Nurse on screen.

[contact] [name] or email [[contact]](mailto:[contact]) for assistance. Note: Randomisation is stratified by site ONLY. The first digit of the randomisation code is the site prefix.

### 4.2 RANDOMISATION CODES & UNBLINDING

Randomisation codes are as detailed above. Randomisation is stratified by site. The trial is open label.

### 4.3 CO-ENROLMENT GUIDELINES

Patients may not be enrolled in any other studies investigating treatment of cryptococcal meningitis, or which may impact on the management of their cryptococcal meningitis as laid down in this protocol. Enrolment in other trials must be discussed with and approved by the TMG and will be at the discretion of the local PIs and under the direction of the site specific local Research Ethics Committees.

## TREATMENT OF PATIENTS

### 5.1 BASELINE ASSESSMENT

#### i) Clinical:

Age, Sex

Significant past medical history, Drug history, time on ART and adherence assessment (if on ART)

Symptoms and duration

Physical examination

#### ii) Laboratory:

- Full blood count (FBC), urea, creatinine, electrolytes, alanine transaminase (ALT)
- HIV serology – if status not already known (with documentation of result)
- CD4 count, and VL if on ART as is routine at the site(s)
- Pregnancy test – urine or serum in women of reproductive age
- CSF: opening pressure, cell count and differential, protein, glucose, India ink, quantitative fungal culture, routine culture, cryptococcal antigen

### 5.2 ANTIFUNGAL DRUG TREATMENT

#### 5.2.1 DRUG REGIMENS

Patients will be randomised to one of two study regimens:

1. L-AmB 10 mg/kg day 1 (single dose) given with fluconazole 1200mg/day plus flucytosine 100mg/kg/d for 14-days
2. Amphotericin B deoxycholate 1 mg/kg/d for 7-days given with flucytosine 100mg/kg/d followed by fluconazole 1200mg/day for 7-days (standard dose, “control arm”)

All patients receive fluconazole 800 mg/d to 10 weeks (provision will be ensured throughout the trial), and 200 mg/d thereafter (as per national guidelines at the site). ART will be commenced 4 – 6 weeks after initiation of antifungal therapy.

Initial intensive phase (first 2 weeks): Patients will be admitted to hospital for the initial intensive phase of treatment, with all patients managed as inpatients for at least 7-days. Individuals may be discharged after day 7 and prior to day 14, in which case treatment will be given under close outpatient supervision during the second week of treatment, ensuring compliance to the trial intervention and facilitating close clinical and laboratory monitoring.

Continuation phase (second 8 weeks): Patients will be followed in the outpatient clinic and given medication to take at home.

### 5.2.2 SOURCE OF DRUGS

Fluconazole (Diflucan, Pfizer) will be obtained locally through the Pfizer nationwide donation programme or purchased from a WHO qualified generic manufacturer should donated supplies be insufficient. Flucytosine will be sourced from Meda Pharmaceuticals Inc. Amphotericin B deoxycholate will be sourced from Bristol-Myers Squibb (BMS). L-AmB (Ambisome) is sourced by Gilead Sciences Europe Ltd. Drugs will be shipped directly to the sites following approval from the relevant regulatory authority.

### 5.2.3 DISPENSING

The drugs will be stored in the pharmacy, clearly labelled as trial medication, and segregated from other pharmacy stock. The trial staff will collect the amounts needed from the pharmacy. Detailed records of drugs dispensed and received will be maintained by both the pharmacist and trial staff.

### 5.2.4 DOSE MODIFICATIONS, INTERRUPTIONS & DISCONTINUATIONS

See manufacturer's latest Summary of Product Characteristics (SPC) for L-AmB, Amphotericin, Flucytosine, and Fluconazole for dose adjustments in renal/hepatic insufficiency and management of expected adverse events. The Ambition trial treatment document may also be referenced in the absence of an internet connection.

- <http://www.medicines.org.uk/emc/medicine/1236>
- <http://www.medicines.org.uk/emc/medicine/559>
- <https://www.drugs.com/pro/flucytosine.html>
- [http://www.cipla.co.za/wp-content/uploads/2013/10/sep\\_cipla-fluconazole-50mg.pdf](http://www.cipla.co.za/wp-content/uploads/2013/10/sep_cipla-fluconazole-50mg.pdf)

#### 5.2.4.A Stopping Drug Early

Discontinuation criteria are considered in [Section 5.4 - Protocol Treatment Discontinuation](#)

### 5.2.5 ACCOUNTABILITY & UNUSED DRUGS/DEVICES

Drug stocks will be regularly monitored and the remaining stocks checked against the amount dispensed.

The investigator/pharmacist/investigational drug storage manager must maintain records of the drugs delivery to the trial site, the inventory at the site, the use by each patient.

These records will include dates, quantities, batch/serial numbers, expiry ('use by') dates, and patient's trial numbers. The investigator/pharmacist/investigational drug storage manager will maintain records that document adequately that the patients were provided the doses specified by the protocol and reconcile all investigational product(s) received from the sponsor.

### 5.2.6 COMPLIANCE & ADHERENCE

The first 7-days of the two week induction treatment will be given in a directly observed hospital setting. Patients may be discharged from day 7 at which point they will remain under close outpatient supervision during the second week, ensuring compliance to the trial intervention. Our experience with cryptococcal treatment trials using some of the same sites has shown loss to follow-up at 10 weeks of less than 2% (ACTA study; ISRCTN: 45035509). To obtain accurate and complete follow-up data for 16 weeks after the start of treatment, telephone numbers and addresses will be collected for patients and relatives, regular telephone contact will be made, and financial assistance will be provided to cover travelling expenses. If a patient fails to attend outpatient clinic visits, the study team will visit the home address to assess vital status and if alive make every effort to persuade the patient to attend and continue antifungal and antiretroviral treatment.

Management of raised CSF opening pressure will be clearly documented in the case record forms and any deviation from standard operating procedures will be recorded and justified. Timing of ART initiation or restarting will be documented in CRFs.

Please refer to the trial specific pharmacy SOPs and SPC document for advice on prescribing, IMP formulation, storage, labelling, temperature monitoring, administration, cautions, contra-indications, accountability and returns information.

### 5.3 OTHER TREATMENT

#### 5.3.1 PREHYDRATION AND ELECTROLYTE SUPPLEMENTATION

To minimise the risk of Amphotericin based therapy induced toxicities all patients will routinely receive 1 litre of Normal Saline with 20mmol of KCl infused over 1-2 hours before the L-AmB/D-AmB infusion. This reduces the risk of renal impairment and hypokalaemia. All patients will also be prescribed oral potassium and magnesium supplementation, with 2 tablets twice daily of potassium chloride (Slow-K, 600mg, 8mmol K/tab) and 2 tablets once daily of magnesium chloride (Slow-Mag 535mg, 5.33mmol Mg/tab) for the duration of Amphotericin based therapy and for two days post discontinuation of L-AmB dosing with additional IV or oral supplementation if potassium or magnesium levels drop below normal ranges.

#### 5.3.2 MANAGEMENT OF RAISED CSF OPENING PRESSURE

Patients with an opening pressure greater than 30 cm will have daily lumbar punctures to remove CSF consistent with guidelines (see Standard Operating Procedure).

#### 5.3.3 ANTIRETROVIRAL TREATMENT

Patients who are ART naïve will start ART 4-6 weeks after initiation of antifungal therapy. The ART drugs used will conform to the local treatment protocols in use. Timing of ART is in accordance with local and international guidelines, and is the earliest time-point currently accepted as good clinical practice. Patients who have been exposed to ART will be managed as per a standardised operating procedure including viral load testing, adherence assessment, enhanced adherence counselling, and resistance testing in line with National and site specific guidelines. Treatment switches to second line therapy in individuals failing first line therapy due to suspected drug resistance will be made 4-6 weeks after initiation of antifungal therapy. ART experienced individuals who are not virologically suppressed at baseline will have a repeat viral load at three months after any treatment switch or adherence intervention to ensure either re-suppression or appropriate treatment failure management.

### 5.4 PROTOCOL TREATMENT DISCONTINUATION

In consenting to the trial, patients are consenting to trial treatment, trial follow-up and data collection. However, an individual patient may stop treatment early or be stopped early for any of the following reasons:

- Fulfilment of an early withdrawal criterion. (The early withdrawal criterion for this trial are an ALT>5 times upper limit of normal i.e. > 200 IU/mL, absolute neutrophil count of <500 x 10^6/L; or platelets <50,000x10^6/L on baseline blood testing, and Cryptococcal meningitis not confirmed – see Trial Treatment Document).
- Unacceptable toxicity or adverse event (e.g. development of severe hepatic or renal dysfunction on treatment. For full details see the Trial Treatment Document)

- Intercurrent illness that prevents further treatment
- Any change in the patient's condition that justifies the discontinuation of treatment in the clinician's opinion
- Inadequate compliance with the protocol treatment in the judgement of the treating physician
- Withdrawal of consent for treatment by the patient

As the patient's participation in the trial is entirely voluntary, they may choose to discontinue the trial treatment at any time without penalty or loss of benefits to which they are otherwise entitled. Although the patient is not required to give a reason for discontinuing their trial treatment, a reasonable effort should be made to establish this reason while fully respecting the patient's rights.

Patients should remain in the trial for the purpose of follow-up and data analysis (unless the patient withdraws their consent from all stages of the trial). If a patient is withdrawn from follow-up, refer to [Section 6.6 - Early Stopping of Follow-up](#).

Data will be kept and included for patients who stop follow-up early as long as consent for this is not withdrawn.

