## 6.3 PROCEDURES FOR ASSESSING SAFETY

There is considerable experience with L-AmB doses up to 10 mg/kg/d. In a trial of treatment for filamentous fungal infections with 100 patients per arm, daily dosing at 10 mg/kg/d compared with 3 mg/kg/d, for 14 days, was associated with increased nephrotoxicity. However, rates of doubling of creatinine and of hypokalaemia were still only those seen with the use of conventional D-AmB formulation 0.7 mg/kg/d in cryptococcal meningitis. Single dose and intermittent L-AmB at up to 10 mg/kg/d has been very well tolerated. Serum creatinine and potassium will be monitored at predetermined intervals to ensure any adverse effects are recognised early and appropriate management undertaken. .

Proportions of patients in different arms suffering clinical and laboratory-defined side effects will be compared as well as the mean percent change from baseline of laboratory values in the treatment groups. Mortality by treatment group will be analysed by summary statistics and time to event analyses, unstratified and stratified for possible confounding factors. The frequency and severity of any immune reconstitution reactions, the factors associated with occurrence of reactions and the frequency of further AIDS-related illnesses will also be determined. These parameters will be reviewed during the study by the Independent Data Monitoring Committee (IDMC – see [Section 9.4](#))

Throughout the study patients will be closely monitored for signs and symptoms of drug toxicity. All toxicities leading to temporary or permanent discontinuation of the study therapy, and all Grade 3 or 4 toxicity effects will require thorough investigation with relevant clinical and laboratory tests as clinically indicated. These should be repeated until final resolution or stabilization of the toxicity. All symptoms and laboratory findings will be graded according to severity using the modified Division of AIDS toxicity criteria.

In the event that the day 7 lumbar puncture identifies an increase in colony forming units from baseline this must be reported as an SAE. The co-ordinating centre will be responsible for managing this situation on a case-by-case basis.

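### Protocol section 5.4 prints the baseline ALT withdrawal limit in IU/mL, about 1,000 times too high to equal 5 times the upper limit of normal; the unit should almost certainly be IU/L

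*Protocol*

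**What the plan says.** Protocol section 5.4 (Protocol Treatment Discontinuation) lists the reasons for which a patient may stop trial treatment early or be stopped. The first is meeting an early withdrawal criterion, and the ALT criterion reads "an ALT>5 times upper limit of normal i.e. > 200 IU/mL".

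The same sentence sets two further laboratory limits: "absolute neutrophil count of <500 x 10 6 /L" and "platelets <50,000x10 6 /L on baseline blood testing" (the 6 is an exponent in both). It then refers the reader to the Trial Treatment Document.

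The rest of the protocol says little about ALT. It is measured at baseline (section 5.1) and on days 7 and 14 and at week 4 (section 6.1). The exclusion criteria in section 3.2 contain no ALT limit. Section 6.3 says that symptoms and laboratory findings will be "graded according to severity using the modified Division of AIDS toxicity criteria", but the grading table in the appendix appears in the text at hand only as a heading.

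**The concern.** The gloss offers 200 IU/mL as another way of writing 5 times the ULN. ALT reference limits are normally tens of units per litre, so a limit of 200 units per millilitre looks wrong by three orders of magnitude. Read literally, no patient would reach it, and the absolute limb would never trigger.

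This is a decision limit for individual patients, not background text. Because baseline ALT is not an exclusion criterion, section 5.4 is the only place in the protocol that sets a baseline ALT limit. A wrong unit here could also be carried into site documents or data-entry checks. That is a possibility; nothing in the protocol shows that it happened.

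**Working it through.** **Inputs**

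- Multiple of ULN: 5 (section 5.4).
- Absolute limit as printed: 200 IU/mL (section 5.4).
- Conversion: 1 IU/mL = 1,000 IU/L.
- ALT ULN: not given in the protocol. Assumed to be 40 IU/L, with a range of 30 to 60 IU/L.

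**1. The ULN implied by the gloss.** Implied ULN = absolute limit / multiple = 200 / 5 = 40, in whatever unit the limit carries.

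- As printed: 40 IU/mL × 1,000 = 40,000 IU/L.
- If the unit were IU/L: 40 IU/L.

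The second is a usable reference limit and the first is not.

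**2. The printed limit in the usual unit.** 200 IU/mL × 1,000 mL/L = 200,000 IU/L.

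**3. Size of the error.** Ratio = 200,000 / (5 × ULN).

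| Assumed ULN (IU/L) | 5 × ULN (IU/L) | 5 × ULN (IU/mL) | Printed limit / (5 × ULN) |
|---|---|---|---|
| 30 | 150 | 0.15 | 1,333 |
| 40 | 200 | 0.20 | 1,000 |
| 50 | 250 | 0.25 | 800 |
| 60 | 300 | 0.30 | 667 |

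No ULN in the assumed range brings the printed limit within a factor of 600 of 5 × ULN.

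**4. The other limits in the sentence.**

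- Neutrophils: 500 × 10^6/L = 0.5 × 10^9/L.
- Platelets: 50,000 × 10^6/L = 50 × 10^9/L.

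Both are per litre and of sensible size. The ALT unit is the only one out of scale.

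**5. Other text that might correct it.** The sections on eligibility, baseline tests, the assessment schedule and safety assessment give no ALT unit, ULN or other ALT limit. The amendment log records no change to this line. The Trial Treatment Document and the body of the grading table are not at hand, so whether either gives an ALT limit cannot be checked.

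**The case against.** The best case on the other side is that this is a one-letter slip in an explanatory gloss. The rule itself is the multiple of ULN, which is correct and sits in the same clause, and the number 200 is right. A site would have to convert its laboratory result to IU/mL, and then prefer the gloss to the multiple, before anything went wrong; nothing in the protocol makes that likely. The list in section 5.4 is permissive, and it separately allows stopping for unacceptable toxicity, including severe hepatic dysfunction, or on clinical judgement. ALT is also repeated on days 7 and 14 and at week 4. The Trial Treatment Document may state the limit correctly, and the factor of exactly 1,000 rests on an assumed ULN of 40 IU/L.

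All of this stands, and it limits the weight of the point. It does not make the printed figure right. The text equates two limits that differ by a factor of at least 600 under any ULN in the assumed range, and nothing else in the protocol supplies the correct unit.

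**Conclusion.** The concern holds, as a minor error. The unit in the ALT gloss is wrong, and the factor (1,000 at the central assumption, about 670 to 1,330 over the range) measures the literal text rather than a likely error in practice. The only outside input is the ULN, and the conclusion does not depend on which plausible value is taken.

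The trial's inference is untouched. Section 5.4 keeps patients who stop treatment in follow-up unless they withdraw consent, section 9.5 bases the primary efficacy analysis on the intention-to-treat population, and the sample size in section 9.3 rests on mortality, the margin, alpha, power and losses to follow-up, none of which involves ALT.

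**What to change.** In section 5.4, change IU/mL to IU/L, so that the limit is more than 5 times ULN, that is, more than 200 IU/L. If site laboratories use different reference ranges, it would help to add that the figure of 200 assumes a ULN of 40 IU/L and that the multiple of ULN governs.

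Check that the Trial Treatment Document gives the same limit and unit. This matters because section 5.2.4 allows it to be consulted when there is no internet connection. The cost is a correction to one unit and one document check; no analysis or sample size changes.
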